We plan to conduct a cluster randomized controlled trial evaluating the efficacy of the aforementioned integrated mental health treatment and intimate partner violence prevention intervention as compared with a treatment as usual control group. In Nyarugusu Refugee Camp, the setting of this study, there are 7 zones within which refugees live. These zones are further subdivided into 52 villages. Women’s groups (described in further detail below; section IV. Participants) operate within these villages and will serve as the site of recruitment and the unit of randomization. Women entering the trial will be assessed for symptoms of mental health problems, intimate partner violence and other related constructs at baseline (week 1) and one post-intervention follow-up at week 10. All measurement and data collection is based on self-report indicators reported by the participant. The intervention is designed to last approximately 2 months (8 sessions, once per week for 8 weeks) with full participation in the study lasting 10 weeks (baseline to follow-up).

AIM 4: Conduct a qualitative process evaluation to examine facilitators and barriers to implementation of the research and intervention protocols.

We plan to conduct a qualitative process evaluation of the implementation of the Nguvu intervention and research protocols within the context of the randomized controlled trial described in Aim 3. To do so we will recruit a subset of participants (n=10), both high (n=5) and low attenders (n=5) from the intervention condition to participate in a qualitative interview with a member of the research team to discuss their experience participating in the intervention related to perceived challenges, risks, benefits, operations and acceptability. We will also qualitatively interview the 10 intervention facilitators and their clinical supervisor to identify their perspectives on successes and challenges of the intervention as well as their experiences as a provider of these services. Lastly, we will conduct qualitative interviews with seven representatives from partner agencies and the community advisory board to examine structural challenges to implementation as well as the perceived impact that implementing Nguvu had at the community and organizational level. We estimate that each of these interviews will take approximately one hour to complete and will be delivered by our trained research assistant team.

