Randomization and Intervention: Given that this is a cluster-randomized trial, the randomization of women’s groups (unit of randomization) will occur prior to recruiting any participants. Thus, if a participant completes the baseline assessment, the intervention team (which works independently from the research team) will identify whether that person belongs to a women’s group that has been randomized to the intervention (vs. control) condition. If in the intervention group, a member of the intervention team will make contact with the participant and schedule their first intervention session. There will be eight sessions that take place once per week for eight weeks.

Follow-up Interview: The week following the intervention, the participant is then asked to complete a follow-up interview. If the participant belongs to a control women’s group then all procedures, with the exception of the intervention, will be the same.

Process Evaluation: A subset of participants will participate in a qualitative process evaluation. In addition to this subset, members of the research and intervention team as well as representatives from partner agencies will be recruited to provide their experience with the implementation of Nguvu.

Responsibilities of the Research and Intervention Personnel: As mentioned above (in Randomization and Intervention), the research assistants and intervention facilitators are expected to work independently to preserve blinding of research assistants to participant’s study assignment. Thus, the research and intervention teams are managed separately with Muhimbili University of Health and Allied Sciences (co-investigators [name] and [name]) responsible for managing the research team and the International Rescue Committee (co-investigator [name]) responsible for managing the intervention team. Johns Hopkins (principal investigator [name]) is responsible for overseeing management across both teams and coordinating their activities. A summary of activities and which teams are responsible for implementation of these activities throughout the duration of the study is displayed below.

| **Study Activity (in chronological order)** | **JHU** | **MUHAS** | **IRC** |
| --- | --- | --- | --- |
| Randomization of women’s groups | X |  |  |
| Recruitment of participants |  | X |  |
| Screening of participants |  | X |  |
| Baseline assessment |  | X |  |

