| 6. CPT | Power, control and self-esteem | - Introduction to power/control issues related to self and others - Challenging questions for control issues - Self-esteem - Caring related to self and others | Daily practice of ABCs, thinking questions and changing thoughts; self-care |
| 7. CPT | CPT Review | - Discussing the impact of distressing events - Planning for the future | Daily practice of ABCs, thinking questions and changing thoughts; self-care; revise safety plan; relaxation exercise |
| 8. Empowerment/ Advocacy | Review of advocacy and safety plan | - Review safety plan - Advocacy - Coping and support methods | -- |

1. Describe the expected duration of the study from the perspective of the individual participant and duration overall.

The total duration of participation in the study is 10 weeks as described below:

| Week | 1 | 2 | 3 | 4 | 5 | 6 | 7 | 8 | 9 | 10 |
| --- | --- | --- | --- | --- | --- | --- | --- | --- | --- | --- |
| Intervention Participant | T0  T1 | S1 | S2 | S3 | S4 | S5 | S6 | S7 | S8 | T2 |
| Control Participant | T0  T1 |  |  |  |  |  |  |  |  | T2 |

T0: Screening, T1: Baseline; T2: Post-intervention interview; S1-S8: Intervention Session 1-8

1. Provide a brief data analysis plan and a description of variables to be derived.

The two primary outcomes of interest are: 1) psychological distress, and 2) intimate partner violence. Psychological distress is operationalized as the total score on self-reported symptom checklists (administered through an interview), the Hopkins Symptom Checklist and the Harvard Trauma Questionnaire, describing depressive, anxiety and post-traumatic stress symptomatology respectively. These measures were selected based on a preliminary qualitative consultation in the refugee camp. Intimate partner violence will be measured using the Demographic and Health Survey Domestic Violence Module that incorporates questions from the Conflict Tactics Scale and World Health Organization Violence Against Women Instrument. Our secondary outcome of interest is functional impairment, which is measured using items developed from formative, qualitative research.

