- Will you use a placebo or non-treatment group, and is that justifiable?

We will use a treatment as usual control group. The separate components of this intervention (Cognitive Processing Therapy, Empowerment Counseling) have been tested in women affected by gender-based violence; however, this study is the first to evaluate these components in an integrated format and also the first to do so in a refugee population. Current services are available for intimate partner violence and some, although fewer, also exist for mental health in the camp. We do not have enough information at this point in time to know whether one study condition is superior to the other, but hypothesize that our more structured and intensive intervention (with specific cognitive therapy elements) will be more effective.

We will also facilitate referrals as appropriate for both the intervention and control group. If participants are experiencing suicidal ideation, severe psychological distress/mental health problems or report serious safety threats during the assessments or intervention the research assistants/intervention facilitators are instructed to refer them to IRC counselors for further assessment, case management and referral to the Tanzania Red Cross or another appropriate agency. During the Abuse Assessment Screen (AAS), which is the measurement tool used in the screening to evaluate past-year history of IPV, participants are instructed to refer them to the appropriate services, which is also IRC counselors and case managers. Unfortunately, this constitutes the formal services available in the camp for IPV survivors and related psychological distress. Therefore we believe that providing the control group with information about how to seek care through IRC, even if they don’t meet criteria for severe mental disorder, imminent risk of suicide or a severe safety threats (which would constitute a referral from the research assistant/intervention facilitator), is most appropriate and what we are able to offer at this time. We have intentionally selected existing IRC counselors as the intervention facilitators such that if the intervention shows evidence of efficacy, they may integrate this intervention into their standard practices which would be available to all women in Nyarugusu.

- Explain when you may remove a participant from the study.

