There are a few situations in which we may remove a participant from this study. This information is also presented to the participant during the written consent for enrollment discussion. If the participant expresses imminent risk of suicide or serious mental illness, we will remove them from the study because we do not think that the intervention we are testing is suitable to manage these needs. Rather a more specialized level of care may be more appropriate and we have identified referral options in the camp through the Tanzania Red Cross, the agency responsible for health services, that is best equipped to manage these cases.

- What happens to participants on study intervention when the study ends?

The intervention was designed to be relatively short (8-weeks), but comprehensive enough to teach the relevant skills for cognitive processing that can be applied beyond the intervention period. The relatively short duration of the intervention is practical and advantageous in an unstable situation, such as a refugee camp, where there is a lot of mobility and change happening regularly. The last session of the intervention is dedicated to reviewing and re-evaluating participant’s health and safety. All participants are provided with a referral list/resource map of relevant services that are available in the camp and if the intervention facilitators believe that a participant could benefit from ongoing services, they have been instructed to make direct referrals as appropriate. Participants assigned to the intervention condition will continue to participate in the research portion of the study (10 weeks in total)

- Describe the process for referring participants to care outside the study, if needed.

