Our strategy to address the safety risk involves both prevention and screening. For prevention we will design the intervention and research assessment implementation in such a way that identifying the program as an intimate partner violence program is highly unlikely. We are implementing the intervention using existing International Rescue Committee staff. The International Rescue Committee is an international non-governmental organization providing community services to most, if not all, refugees in the camp. We also plan to hold intervention sessions and research assessments in spaces provided by the International Rescue Committee that are normally frequented by women for activities not necessarily related to gender-based violence (e.g. ‘empowerment’ activities, income generation activities, basic literacy training, women’s health issues, etc.). In regards to screening, the intervention facilitators will assess safety during each session. The research team also inquires about intimate partner violence and safety during their assessments. If there is reason to believe that the participant is at an elevated level of risk that requires immediate response, they will refer the participant to existing gender-based violence services, including the women’s shelters and other International Rescue Committee services in the camp according to existing SOPs.

1. Describe the research burden for participants, including time, inconvenience, out-of pocket costs, etc.

The research burden involves 3-4 assessments ranging from 30 minutes to 1.5 hours each. If the participant elects to complete the baseline assessment during the same visit as the screening, they will only have two assessments, which occur at baseline and 10 weeks after enrollment. If they prefer to conduct these interviews on separate occasions the baseline interview will take place within a week from the screening and will be followed by the post-intervention assessment. The only out-of-pocket expense relates to transportation. The camp is quite large and can take approximately one hour to travel by foot from Zone 7 (northwest) to Zone 1 (southeast). If transportation challenges would preclude participation or result in out-of-pocket expenses to a participant, the research team will provide transportation vouchers, but this is not expected to occur.

1. Describe how participant privacy will be protected during data collection if sensitive questions are included in interviews.

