Participant safety will be monitored throughout the study, both by the research team (during assessments) and intervention team (during each session of the intervention). The intervention program is specifically geared towards improving safety of women experiencing intimate partner violence. All study staff and members of partner organizations may note concerns regarding participant safety or other unanticipated problems and adverse events. Concerns can be expressed to the In-Country Program Manager, who will immediately notify an established DSMB. The DSMB will be formed by the In-Country Project Coordinator, a member of the GBV Working Group and the International Rescue Committee. The DSMB will review each case, and formulate recommendations that will be followed-up by the In-Country Project Coordinator. For medical issues, the DSMB will connect with co-investigator [name] (a licensed psychiatrist) and the clinical officer of the Tanzania Red Cross Society – as per existing referral pathways already described in the camp’s GBV SOPs. The DSMB will also determine whether a case forms a serious adverse event (i.e., unanticipated risks in which there is a threat of harm to participants or others, and that are related to the study), in which case the JHSPH and local IRBs (see below) will be notified.

D**.** Reporting unanticipated problems/adverse events (AE’s) to the IRB (***all studies must complete this section***):

Describe your plan for reporting to the IRB and (if applicable) to the sponsor. Include your plan for government-mandated reporting of abuse or illegal activity.

NOTE: The IRB does not require submission for all AEs, only those that are **unanticipated, pose risk of harm to participants or others, and are related to the study**.

Only adverse events that are determined to be serious adverse events (i.e., unanticipated risks in which there is a threat of harm to participants or others, and that are related to the study) by the DSMB will be notified to the JHSPH IRB and local IRBs.

E. Other IRBs/Ethics Review Boards:

If other IRBs will review the research, provide the name and contact information for each IRB/ethics review board and its Federal Wide Assurance, if it has one (available on OHRP’s website at <http://www.hhs.gov/ohrp/assurances>).

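### The removal rule ends study participation rather than only the sessions, and scheduled contacts that can trigger it occur only in the intervention arm, so week-10 outcomes may be lost unevenly by arm

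*Protocol*

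**What the plan says.** **The rule.** Section V.C, under the item on when a participant may be removed, says: "If the participant expresses imminent risk of suicide or serious mental illness, we will remove them from the study". The reason follows directly: "because we do not think that the intervention we are testing is suitable to manage these needs". The item opens by saying that removal may happen and then says that it will.

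**The outcome schedule.** Section III (Aim 3) has women assessed "at baseline (week 1) and one post-intervention follow-up at week 10". The duration table in Section V.C shows eight sessions in weeks 2 to 9 for intervention women and blank cells for control women in those weeks (legend: "T0: Screening, T1: Baseline; T2: Post-intervention interview; S1-S8: Intervention Session 1-8"). For a control woman, Section V.C says that all procedures, "with the exception of the intervention, will be the same".

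**Who can notice a trigger.** Section VII says that "the intervention facilitators will assess safety during each session". The Safety Monitoring section repeats that the intervention team monitors safety at each session and the research team at assessments. Section V.C adds that, for suicidal ideation, severe distress or serious safety threats found "during the assessments or intervention the research assistants/intervention facilitators are instructed to refer them to IRC counselors". Section III (Aim 2) treats suicide risk assessment as part of the safety protocols that apply in the trial.

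**At entry.** Section IV already excludes imminent suicide risk and serious mental illness, so the removal rule acts mainly on states that arise or come to light after enrolment. Women's groups are randomised before recruitment, so these are post-randomisation losses.

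**The concern.** Ending the sessions and ending outcome collection are separate decisions, and the rule merges them. Its reason could explain the first. It does not explain forgoing a week-10 interview, and it has no application to a control woman, who receives no sessions.

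The chance of removal before week 10 then depends on how often a woman is seen, which the protocol fixes differently by arm. If removed women would have scored worse at week 10, their absence lowers the intervention-arm distress mean and makes the intervention look better. Their partner-violence outcome, the other primary outcome, is lost as well. A later analysis plan can test assumptions about uncollected scores but cannot restore them, so the point belongs in the protocol.

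**Working it through.** **1. Is outcome collection kept anywhere for removed women?** One sentence in the same item group says that intervention participants go on in the research part of the study for the full 10 weeks. It answers the prompt on what happens when the study ends, and follows text on the short course and onward referral. It does not mention removed women. No other text covers them.

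**2. Scheduled contacts after baseline and before the week-10 visit that can trigger removal.**

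| | Intervention | Control |
|---|---|---|
| Sessions, weeks 2-9 | 8 | 0 |
| Research assessments, weeks 2-9 | 0 | 0 |

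A random 10% of participants also get a 2-3 minute quality-assurance contact, but its three questions ask only whether and how the assessment took place. At week 10 both arms are seen, but that is the outcome visit itself.

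**3. The plan's own figures (Section III).** Inputs: z-values 1.96 and 0.842, change variance 0.55007, ICC 0.333, difference 1.3 − 0.7 = 0.6, and the cluster size 18.269 that the formula uses (the parameter list gives 10, a separate matter).

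- n = 2 × (2.802)² × 0.55007 × [1 + 17.269 × 0.333] / 0.36 = 161.97, so 162 per group. This reproduces.
- 162 / 0.9 = 180 per group, an allowance of 18 women per arm for all attrition.
- Standard error implied by 80% power: 0.6 / 2.802 = 0.214.
- Week-10 SD: √0.36 = 0.6.

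**4. Size of the shift.** Let a fraction p of the intervention arm be removed, with week-10 scores that would have averaged δ above the rest. The observed mean is too low by p × δ. Both p and δ are assumptions; δ is taken as 1-2 SD, that is 0.6-1.2.

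| p (women of 180) | p × 0.6 | p × 1.2 | share of 0.6 | in SE of 0.214 |
|---|---|---|---|---|
| 1% (1.8) | 0.006 | 0.012 | 1-2% | 0.03-0.06 |
| 1 in 30 (6) | 0.020 | 0.040 | 3-7% | 0.09-0.19 |
| 5% (9) | 0.030 | 0.060 | 5-10% | 0.14-0.28 |

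The middle row borrows the 1 in 30 that Section VII expects to have distress serious enough to stop an interview. It is not a removal rate and serves only as an illustration.

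**5. Second model.** If removal acts on a latent severity correlated r with the week-10 score, the shift is r × 0.6 × φ(z_p)/(1 − p). For r from 0.3 to 1.0 this gives 0.005-0.016 at 1%, 0.014-0.046 at 3.3% and 0.020-0.065 at 5%, the same order as step 4.

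**6. Removal in control.** If a fraction q is also removed in control with the same excess, the shift is (p − q) × δ. For p = 5% and q = 1% it is 0.04 × 0.6 = 0.024 to 0.04 × 1.2 = 0.048.

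**7. What the mixed model recovers.** A removed woman contributes her baseline score only. If the change variance was built from the two listed variances in the usual way, 0.25 + 0.36 − 2ρ(0.5)(0.6) = 0.55007 gives a baseline-to-follow-up correlation of 0.05993 / 0.6 ≈ 0.10. On those planning values baseline predicts little of the week-10 score.

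**The case against.** Several points on the other side are sound.

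- **The rule may mean less than it says.** Removal from the study is not defined, the phrase echoes the form's prompt, and the reason is about the intervention. The sponsor may have meant stopping sessions only. That stands as a possible reading, and it is a reason to say so in the text: as worded, field staff could properly stop follow-up.
- **Control is not blind to these events.** A reader might infer that they go undetected in control. The documents do not support that. Control women get referral information and may use existing services, and any study staff or partner-organisation member may raise a concern. The difference is between scheduled and unscheduled detection.
- **Weekly detection is partly inferred.** The per-session check in Section VII concerns safety from partner violence. Suicidality enters through the referral instruction in Section V.C and the safety protocols in Section III, and that instruction prescribes referral, not removal.
- **Not every trigger is the top of the distress scale.** Section IV describes serious mental illness as intellectual disability, psychotic or manic symptoms and severe substance use. These are not the upper end of depressive, anxiety and post-traumatic scores. Only suicide risk plausibly is.
- **The mixed model helps somewhat.** Baseline scores stay in the model, so p × δ leaves out whatever selection baseline predicts. Step 7 suggests that this is little on the planning values.
- **Removed women may improve.** They are referred to more specialised care, so a week-10 excess of 1-2 SD is not assured.

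A reader might also infer that a suicidality comparison is lost at week 10. None is planned: the stated outcomes are distress, partner violence and functional impairment, and adverse events go to the DSMB. None of these points removes the eight-to-none difference in scheduled contacts or keeps the week-10 outcome for removed women.

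**Conclusion.** The point holds in a limited form. As written, the rule ends study participation for a reason that bears only on the intervention, nothing preserves the week-10 outcome, and scheduled opportunities to trigger it before week 10 exist in one arm only. The loss would be uneven by arm and related, at least for suicide risk, to the distress outcome. It most plausibly favours the intervention.

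The size cannot be fixed from the protocol. With 1-5% removed in one arm and a week-10 excess of 0.6-1.2 points, the shift is 0.006-0.06 points, 1-10% of the planned difference and at most about 0.3 of the implied standard error. Some removal in control, or improvement after referral, would make it smaller. The shift in points does not depend on the true effect, so its share grows if the effect is below 0.6. The documents do not support calling this a large bias. The case for correcting it rests on its systematic direction, the single post-baseline measurement and the low cost of a correction made before the data are lost. The direction for partner violence is not quantified.

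**What to change.** Leave referral and all decisions about sessions as the clinical text has them. Reword the removal item in Section V.C so that it separates stopping the sessions from stopping outcome collection:

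- stopping the sessions does not by itself end outcome collection;
- the week-10 interview is still sought where it is judged safe and the woman agrees;
- she is analysed in her assigned arm;
- removals, with reason and timing, are reported by arm;
- a sensitivity analysis covers missing week-10 scores, for example by giving removed women scores worse by a stated range such as the 0.6-1.2 points used above.

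If the sponsor intends that some women give no further data, the item should say so and the expected loss by arm should be acknowledged.

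Cost: one protocol sentence, matching consent wording with IRB review (the removal terms are presented at written consent), and a few sensitive interviews of about 1.5 hours under the existing distress procedures. The sample size is unaffected.
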